
### Environmental Factors During Field Tests

To keep the temperature difference between the field tests and the spiroergometry in the laboratory as little as possible, the laboratory test will be carried out at a standardized room temperature of 20°C, which corresponds with the expected average daily temperature of the study months in the test regions. Should temperatures exceed 26°C, the tests will be postponed since a relevant impact on the heart rate response would be expected [17]. Moreover, humidity will be recorded.

### CTTT (1 km)

The CTTT will be implemented outdoors in Werfenweng, Austria, and Aschau im Chiemgau, Germany. The maps and height profiles of the chosen trails for the CTTT are shown in Figure 2. The CTTT includes an easily accessible path with a length of 1000 (SD 100) meters and an elevation of 100 (SD 30) vertical meters, as well as a gradient of up to 26%.

After completing the laboratory test, all participants who have passed the baseline examination (no relevant heart diseases found during testing) will be invited for the field testing. This submaximal cardiorespiratory fitness test will be performed on the 1-km CTTT by each participant alone, with a researcher walking beside the participant. After an explanation of the route, as well as how to walk the track, the participants will get equipped with the measuring devices using the same setup as that during the treadmill test, except for the 12-lead ECG device. They will be wearing the portable K5 device operating in DMC mode, the Garmin chest strap, which will send their heart rate to the K5 device, and the Garmin Vivoactive 4 smartwatch set for wrist-based heart rate measurement. The outdoor exercise test should not be an all-out assessment but rather a submaximal assessment. A researcher will individually accompany participants (walk by their side) and guide their intensity via the Borg scale. Participants will be instructed to hike at a brisk pace and adjust their walking speed according to the trail’s steepness. They will be further required not to reach >15 RPE on the Borg scale. Individual Borg values will be assessed at multiple stages of the CTTT, and the pace will be adjusted accordingly if the RPE value exceeds 15 or falls below 11.

**Figure 2 figure2:**
[figure not shown]
Cardio trekking test trail profiles. (A) Map of the cardio trekking test trail in Werfenweng, Austria. (B) Map of the cardio trekking test trail in Aschau im Chiemgau, Germany. (C) Profile of the Austrian trail. (D) Profile of the German trail.

### Field Test Involving 8-km Hikes

The 8-km hikes were selected based on touristic, sport scientific, and medical aspects like accessibility, visitor frequency, difficulty, soil texture, important landmarks for sightseeing, etc. Moreover, proximity to the selected CTTT plays an essential role in choosing the tracks. The maps and height profiles of the chosen trails for the long hikes are shown in Figure 3. The selected course in Austria has a length of approximately 8400 m, with 402 vertical meters uphill and 461 vertical meters downhill, and the steepest passage has a 37% gradient. The German trail has a length of approximately 8200 m, with 415 vertical meters uphill and 410 vertical meters downhill, and the steepest passage has a 26% gradient.

For the clinical study, we plan for at least one-third of all participants to hike the 8-km trail wearing the portable K5 device in the DMC mode. The Garmin chest strap sends heart rate data to the K5 device, and the Garmin Vivoactive 4 smartwatch is set for wrist-based heart rate measurement. All participants, who will hike the long trail without the K5 device, will track their hike using a Garmin chest strap connected to the Garmin Vivoactive 4 smartwatch. The groups for the long hike will vary in group size from 2 (1 researcher and 1 participant) to 6 (1 researcher and up to 5 participants). Intensity on the 8-km hike will be moderate. The participants will get individual heart rate ranges based on their ventilatory thresholds assessed during the laboratory treadmill test. Throughout the hike, the heart rate should remain in that range. In addition, the researcher will determine RPE occasionally, which should not exceed a value of 15 on the Borg scale.

**Figure 3 figure3:**
[figure not shown]
Cardio trekking trail profiles. (A) Map of the cardio trekking trail in Werfenweng, Austria. (B) Map of the cardio trekking trail in Aschau im Chiemgau, Germany. (C) Profile of the Austrian trail. (D) Profile of the German trail.

### Cartography of the 8-km Cardio Trekking Trails

Subsequent to the 8-km hikes with the study participants, we will perform additional “cardio hikes” for tourists to gain further data for georeferencing and cartography of the selected hikes. We aim to complete guided hikes for 250 willing participants in both countries. All participants will be outfitted with heart rate sensors (Polar Verity Sense arm strap or Garmin Vivoactive 4 smartwatch) for tracking their heart rate, speed, etc, during the hikes. The selected 8-km cardio hikes in Austria and Germany will be newly mapped based on the data from our study participants. This part of the project will aim to tone the hike sections according to heart rate.

### Primary and Secondary Outcomes

#### Primary Outcome

The primary outcome is estimating the exercise capacity based on physiological features, subjective performance parameters, and route characteristics collected for 2 cardio trekking test routes in Werfenweng, Austria, and Aschau im Chiemgau, Germany. The 2 test routes have a length of approximately 1 km and a gradient of up to 26%. Participants will hike 1 of the 2 test routes shortly after the laboratory measurement. Based on these data and in combination with the capacity of maximal oxygen uptake (VO_2max_) derived in the laboratory setting, a statistical model for the prediction of VO_2max_ will be developed.

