### Statistical Analysis

#### Sample Size Calculation

The sample size calculation was done with G*Power Software (Version 3.1.9.7; Heinrich-Heine University) [18,19]. With α=.05, β=.1, and a middle effect size of *f²*=0.15, a strong model should be created. The calculation of maximal oxygen uptake could be performed using a linear multiple regression model with 6 predictors. For a model power of 0.90, 123 participants would be required to finish the study. To make sure we reach the number we chose, we added a 15% dropout rate and set the target sample size to 144 participants, with a balanced distribution in Austria and Germany.

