#### Estimation Model for Exercise Capacity

As the first step in model development, the data collected in the laboratory and the results from the 1-km CTTT and 8-km hike will be analyzed descriptively to identify anomalies in the data, such as outliers or data loss due to possible device crashes. Based on these analyses, the data for Austria and Germany will be cleaned.

Following the principle “from the lab to the field,” the first estimation model will be developed based on features collected in the laboratory to verify how accurate and reliable VO_2max_ can be estimated. When the proof of concept works on the laboratory data, an in-field estimation model will be created based on the CTTT measurements to see if VO_2max_ from the laboratory can be determined based on the data collected on the CTTT. The derived estimation models will be validated with cross-validation and evaluation metrics (eg, adjusted R-squared and mean absolute error).

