Similar to our study, Chiaranda et al [25] developed an equation for a 1-km submaximal treadmill test for patients with cardiovascular diseases. They recommend it as a possible substitute for maximal exercise testing at laboratories in rehabilitation and health and fitness facilities where expense, space, time, and personnel needed to carry out these cardiopulmonary tests are limited. They also tried to reproduce this 1-km flat submaximal walking test in an outdoor setting with similar results [26]. However, their equations only apply to cardiac patients. We set out to develop an equation for healthy individuals interested in hiking, which is one of the most common leisure activities in mountainous areas. We aim a step further as we hope to integrate this equation into existing hiking apps to deliver individual recommendations based on the performance at a standardized CTTT. In addition, the Connect2Move project hopes to disseminate the characteristics of the developed equation and CTTT throughout interested mountainous areas.

As the interest in green tourism and holidays focusing on health increases, we aim to deliver cost-effective easily accessible tools that facilitate individual recommendations for hiking tours and help avoid overexertion, resulting in fewer cardiovascular events while hiking.

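### Route characteristics in the primary VO2max model give one between-trail contrast, fully aliased with country and laboratory, so the data cannot show that the equation transfers to a third trail

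*Protocol article*

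**What the plan says.** The Primary Outcome section of the protocol article names three groups of inputs to the VO2max model: physiological features, subjective performance parameters, and "route characteristics collected for 2 cardio trekking test routes in Werfenweng, Austria, and Aschau im Chiemgau, Germany". It adds: "Participants will hike 1 of the 2 test routes". No crossover between trails is described.

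The Recruitment Process and Measurement Process section splits the sample equally between Austria and Germany. The Study Design section assigns Austrian participants to the Salzburg laboratory and German participants to the one in Prien am Chiemsee.

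On validation, the section Estimation Model for Exercise Capacity describes one in-field model and says: "The derived estimation models will be validated with cross-validation and evaluation metrics". It gives no fold scheme and mentions no further trail.

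The intended use is wider than two trails. The Introduction wants a test trail that mountain areas can set up for themselves, and the Discussion hopes to "disseminate the characteristics of the developed equation and CTTT throughout interested mountainous areas" and to build the equation into hiking apps.

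**The concern.** A route characteristic can have its own effect estimated only if it varies separately from everything else that differs between the groups. Here it does not. Everyone on a given trail meets the same length, ascent and profile, and contributes one laboratory VO2max. The only variation in route-level features is the difference between the two trails, and that is also the difference between two countries, two laboratories and two recruited populations.

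Two things are at stake. First, a fitted route term would have no clear meaning: a calibration difference between laboratories, a population difference not captured by the individual predictors and a true trail effect all look the same. Second, an error estimate from within these two sites says how well the equation works for new people on these trails. It does not say how well it works on a trail the model has never seen, which is the use the project hopes for. The predicted VO2max also feeds the personalised intensity levels on the digital map, so an offset would carry into those.

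**Working it through.** **1. The plan's own figure.** The Sample Size Calculation section gives: "With α=.05, β=.1, and a middle effect size of *f²*=0.15", a calculation "using a linear multiple regression model with 6 predictors", and "For a model power of 0.90, 123 participants would be required to finish the study". For the overall F test that R² = 0, the noncentrality is λ = f² × N = 0.15 × 123 = 18.45, with 6 and 123 − 7 = 116 degrees of freedom. Power at N = 123 is 0.9012, and 123 is the smallest N that reaches 0.90. For 15% dropout, 123/0.85 = 144.7 and 123 × 1.15 = 141.5, so the stated 144 is consistent. The sample size is not in error. It tests whether the predictors together explain anything and is silent on transfer between trails.

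**2. Rank of the route and site columns.** Take seven columns: intercept, route length, ascent, gradient, country, laboratory, population. Every participant's row is one of only two distinct vectors, so the rank is at most 2. A numerical check with 72 people per trail and placeholder trail values gave rank 2 of 7 columns. The actual profiles are in a figure that is not shown, but the result does not depend on them. After the intercept, one degree of freedom remains for all six other columns. More participants would not change this. A feature that is equal on both trails is constant and has no estimable effect at all. Gradient does vary between sections of a trail, but everyone on that trail meets the same sections, so this does not separate trail from site.

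**3. What cross-validation within the two sites can see.** The documents give no VO2max SD and no between-trail SD, so this step is illustrative. Assumptions: VO2max mean 35 and SD 7 mL/kg/min; a field predictor equal to VO2max plus a trail or site offset (SD τ between trails) plus noise of SD 4; 72 people per trail; 10 folds that mix both sites; a site term in the pooled model.

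- Slope of VO2max on the predictor within a trail: b = 49/(49 + 16) = 0.754.
- Residual variance within a trail: 49 × 16/65 = 12.06.
- Mean absolute error for a normal error: 0.798 × SD. Within the two trails: 0.798 × √12.06 = 2.77, whatever τ is.
- Fit on one trail, test on the other: error variance 12.06 + 2b²τ². At τ = 4: 12.06 + 18.19 = 30.25, and 0.798 × 5.50 = 4.39.
- A third trail, with the site term set midway: error variance 12.06 + 1.5b²τ². At τ = 4: 12.06 + 13.64 = 25.70, and 0.798 × 5.07 = 4.04.

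The simulation (400 replicates) agrees to within simulation error. Mean absolute errors in mL/kg/min:

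| τ | Mixed 10-fold | Other trail | Third trail |
|---|---|---|---|
| 0 | 2.79 | 2.80 | 2.78 |
| 2 | 2.80 | 3.32 | 3.19 |
| 4 | 2.79 | 4.45 | 4.06 |
| 6 | 2.81 | 5.67 | 5.13 |

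The mixed-fold error stays flat while the error on an unseen trail rises with τ. If τ were 0, the mixed-fold error would suffice, but two trails cannot establish that.

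**The case against.** **The validation text does not fix any folds.** This stands. A reader might infer that the plan mixes both trails in every fold and so rules out any test across sites. The article does not say so. Fitting on one country and testing on the other is itself a form of cross-validation, and fold detail is commonly left to a fuller document. The fault lies in having two trails aliased with site, and no fold scheme removes it.

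**No free route coefficient is named.** This stands in part. The six predictors are not listed, and route data could enter as slope-normalised performance. But the primary outcome does list route characteristics as an input group of their own, so the plan leaves the unestimable version open.

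**The sites are harmonised.** Both use the same portable spirometry device and mode, treadmill protocol, laboratory temperature and eligibility criteria, and different staff practice by country is not documented. This makes a large site offset less likely. It does not separate trail from site.

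**The size can be overstated.** A reader might take an assumed 3–5% laboratory or population difference at 35 mL/kg/min, that is 1.05–1.75 mL/kg/min, as a false route effect carried to every new trail. The documents support neither figure. Individual predictors such as heart rate and speed would absorb part of a population difference, and a coefficient on route features shifts a prediction according to the new trail's features, not by a constant. Likewise, reading "a length of 1000 (SD 100) meters and an elevation of 100 (SD 30) vertical meters" as a permitted range of 70–130 m ascent is an interpretation, since the text prints SD. Nothing here depends on it.

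**Testing across the two sites does not isolate the trail.** This stands. It gives only two folds, each trained on about 144/2 = 72 people against the 123 in the sample size section, and it still mixes trail with laboratory and population. A good result would not prove transfer.

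**Conclusion.** The point holds at moderate severity. Route-level length, ascent and gradient give at most one between-trail contrast, fully aliased with country and laboratory. A residual site offset would therefore be read as a route effect, and validation within the two sites cannot by itself support use on a third trail. The aliasing rests on one inference: that each laboratory's participants walk the trail in the same country. The article does not say this outright, but the Study Design and recruitment sections together imply it. The size of any offset cannot be derived from the documents; the simulated errors only show the direction under assumed SDs.

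A reader might go further and conclude that the primary analysis is invalid as it stands. The documents do not support that. The primary outcome is framed around these two trails, and dissemination is expressed as a hope. A model built on individual predictors can still be estimated and checked for new people on these trails. What cannot be supported is an interpretable route effect or a claim of transfer.

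**What to change.** Four changes to the analysis and its reporting:

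1. Do not fit route-level length, ascent or gradient as free predictors of VO2max.
2. Express performance on the 1-km trail in trail-normalised form, for example vertical speed, or heart rate at a given vertical speed on GPS segments. The Methods paragraph of the Abstract says speed, GPS location and altitude are recorded, so no new data are needed.
3. Beside the planned cross-validation, report the site offset after the individual predictors, and the error and calibration from fitting on Austria and testing on Germany and the reverse. Label this a stress test that still mixes trail with site.
4. Limit the conclusion to these two trails until a further trail is tested, even if no offset appears.

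The Results section reports that 144 people had already been tested outdoors by the end of April 2022, so the remedy has to be analytic. The cost is revised wording and one extra validation run. The downside is small training sets of about 72 and a reported error that will probably look less favourable.

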#### Secondary Outcome

During the 8-km hiking tour, the cardiovascular load will be measured on defined hiking sections (ascents, descent, and plain levels). Based on the individually predicted VO_2max_ on the 1-km CTTT, the estimated cardiovascular load (heart rate or oxygen cost) will be defined and visualized in a digital map using 3 different intensity levels (low, moderate, and high intensity).

#### Accuracy of Heart Rate Measurements

Each participant’s heart rate will be measured simultaneously from at least two different sources during every part of the study. We aim to evaluate the accuracy of the wrist-based Garmin Vivoactive 4 smartwatch data and Garmin chest strap data considering the gold standard 12-lead ECG data measured during the treadmill test. Further, the wrist-based measurement accuracy during the field tests will be compared with the chest strap measurement accuracy.

#### Comparison of Resting Evaluation Versus Exercise Test for Exercise Capacity

We will measure the maximal exercise capacity (VO_2max_) during the use of the modified Bruce protocol on the treadmill. As we will use the portable spirometry device K5 from Cosmed, we will be able to use the DMC method instead of the breath-by-breath measurement.

As we will obtain measured VO_2max_ values, we will be able to compare those results with estimations for this parameter, which we will obtain with the Polar Fitness Test. This test is a 5-min resting evaluation performed with a chest strap and the Polar beat app. Based on the measured heart rate variability and added data like age, gender, weight, height, and fitness classification, the app will estimate the individual’s VO_2max_.

In addition, we will obtain VO_2max_ estimation based on the outdoor hikes that involve recording with the Garmin Vivoactive 4 smartwatch.

We aim to evaluate the validity of the 2 VO_2max_ estimations.

#### Physical Activity and Quality of Life

We will use the IPAQ short form to assess participants’ physical activity levels. The questionnaire captures vigorous, moderate, and walking activities and sitting times of the previous 7 days.

The SF-36 will be used to assess health-related quality of life. It contains 36 items grouped into the following 8 dimensions: physical functioning, physical role, body pain, general health, vitality, social functioning, emotional function, and mental health.

### Statistical Analysis

#### Sample Size Calculation

The sample size calculation was done with G*Power Software (Version 3.1.9.7; Heinrich-Heine University) [18,19]. With α=.05, β=.1, and a middle effect size of *f²*=0.15, a strong model should be created. The calculation of maximal oxygen uptake could be performed using a linear multiple regression model with 6 predictors. For a model power of 0.90, 123 participants would be required to finish the study. To make sure we reach the number we chose, we added a 15% dropout rate and set the target sample size to 144 participants, with a balanced distribution in Austria and Germany.

#### Descriptive and Statistical Significance

Statistical evaluations of the hikes (per region or participant) will be performed. Since this study aims to develop a model for calculating exercise capacity during a hiking field test, the statistical analysis will be performed on a per protocol basis, thus including only participants who complete the lab test, the 1-km CTTT, and the 8-km hike. Statistical analyses will be performed using SPSS version 24.0 (SPSS Inc) and R version 4.1.0 (The R Project for Statistical Computing).

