### Recruitment Process and Measurement Process

The recruitment of participants will be conducted using the different information channels of the included institutes via the project website, recruitment flyers, and word-of-mouth advertising. If potential participants are >45 years of age, they will be informed about the study objectives, evaluation protocol, and procedures. On agreeing to participate, they will be invited to the initial laboratory testing at 1 of the 2 testing sites. At the beginning of the initial testing, researchers will provide detailed information about the study again, and the participants will be asked to read and sign written informed consent.

Participants will have to perform 3 different exercise testing procedures to complete the study, including 1 laboratory test on a treadmill and 2 field tests (1-km CTTT and 8-km hikes) in Werfenweng, Austria, or Aschau im Chiemgau, Germany. There will be at least 1 full day of rest between the laboratory test and the first field test. The 1-km CTTT and 8-km hikes will be performed on 2 days. If the scheduling of 2 days is not possible, the 1-km CTTT and 8-km hikes will be conducted on the same day with at least 1 hour of rest in between. Half of the study population will participate in Austria, and the other half will participate in Germany.

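### The single per-protocol set requires the 8-km hike, which the primary VO2max model does not use, so valid laboratory-plus-CTTT pairs are dropped and fitter people may be selected

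*Protocol article*

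**What the plan says.** Under Descriptive and Statistical Significance, the protocol article defines one analysis population. The analysis is per protocol, "thus including only participants who complete the lab test, the 1-km CTTT, and the 8-km hike". The reason given is that the study develops a model of exercise capacity from a hiking field test. No other set is named for any outcome.

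The primary model is described in two places.
- Primary Outcome takes data from the two test routes of about 1 km and links them to the laboratory value: "Based on these data and in combination with the capacity of maximal oxygen uptake" from the laboratory, a prediction model for VO2max is developed.
- Estimation Model for Exercise Capacity says that "an in-field estimation model will be created based on the CTTT measurements", to see whether laboratory VO2max can be recovered from them.

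The 8-km data have a different use. Under Secondary Outcome, "During the 8-km hiking tour, the cardiovascular load will be measured on defined hiking sections", and the sections on trail definition and visualization build on that. In the model section, 8-km results appear only in the initial descriptive check for outliers and data loss.

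**The concern.** An analysis set should require the data that its analysis needs. A participant with a valid laboratory test and a valid CTTT supplies both the outcome and the predictors of the primary model. Whether that person also finished the 8-km hike adds nothing to the fit, yet it decides whether the pair is used.

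Losing pairs costs some precision. The larger risk is selection. The 8-km trails are about 8.2 to 8.4 km long with 402 to 415 m of ascent, against about 1 km and 100 m for the CTTT. Low fitness is therefore a plausible reason for not finishing. If it operates, the set is conditioned on something related to VO2max, the very quantity being predicted. Truncating the low end of the outcome flattens the slope and raises predictions for unfit people. For a tool meant to prevent overexertion, that error runs in the unhelpful direction. The equation is to be applied to people who have walked only the test trail, so its users will include people who would not have finished the longer hike.

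**Working it through.** **1. Which data each analysis uses**

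| Analysis | Laboratory | 1-km CTTT | 8-km hike |
|---|---|---|---|
| Primary VO2max model | yes (outcome) | yes (predictors) | no |
| Section load and map | thresholds | predicted VO2max | yes |
| Stated analysis set | required | required | required |

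The third requirement does not match the first row.

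**2. The plan's own sample size**

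Inputs from Sample Size Calculation: alpha 0.05, power 0.90, f² = 0.15, 6 predictors, 15% dropout. The check is the noncentral F test of R2 against zero, with lambda = f² × N and df = (6, N − 7).
- N = 123: lambda = 0.15 × 123 = 18.45, df = (6, 116), power 0.901.
- N = 122: power 0.898. So 123 is the smallest adequate number, as stated.
- Dropout: 123 / 0.85 = 144.7, against the stated 144. The difference is immaterial.

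**3. Power under losses between the CTTT and the 8-km hike**

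The article reports 144 people tested outdoors. Assume that all 144 have a valid CTTT. The loss rates are assumptions, since the article gives none.

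| Assumed loss | N | Power |
|---|---|---|
| 0% | 144 | 0.948 |
| 5% | 136 | 0.933 |
| 10% | 129 | 0.917 |
| 15% | 122 | 0.898 |
| 20% | 115 | 0.876 |

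Since 144 − 123 = 21, up to 21 people (21/144 = 14.6%) can be lost with power still at least 0.90.

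**4. Selection, worst case**

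Assumptions: VO2max y and one composite predictor x are standardized, with true R2 = 0.60, so the slope is √0.60 = 0.775. Exactly the lowest 10% on y are lost. The cut is at z = −1.2816, where the normal density is 0.1755.
- Retained mean of y: 0.1755 / 0.9 = 0.195.
- Retained variance of y: 1 − 1.2816 × 0.195 − 0.195² = 0.712 (SD 0.84).
- Retained covariance: 0.775 × 0.712 = 0.552.
- Retained variance of x: 0.60 × 0.712 + 0.40 = 0.827.
- Slope in the selected set: 0.552 / 0.827 = 0.667, which is 0.86 of the true slope.
- Intercept: 0.195 − 0.667 × (0.775 × 0.195) = 0.094.
- Excluded group: mean y = −0.1755 / 0.1 = −1.755; mean x = 0.775 × (−1.755) = −1.36.
- Over-prediction there, model fitted to everyone: 0.775 × (−1.36) + 1.755 = 0.70 SD.
- Over-prediction there, model fitted to the selected set: 0.094 + 0.667 × (−1.36) + 1.755 = 0.94 SD.
- Added by the restriction: 0.94 − 0.70 = 0.24 SD.

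A simulation with 2,000,000 draws gives the same result (0.701 to 0.943 SD; R2 in the selected set 0.516).

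**5. Sensitivity to the assumptions**

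Extra over-prediction in the excluded group, from the same simulation:

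| True R2 | 5% lost | 10% lost | 15% lost |
|---|---|---|---|
| 0.13 (implied by f² = 0.15) | 0.14 SD | 0.24 SD | 0.32 SD |
| 0.60 | 0.16 SD | 0.24 SD | 0.31 SD |

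The result depends mainly on the share lost and hardly at all on R2.

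**The case against.** The strongest reply is that no harm is documented. The article counts both the CTTT and the 8-km hike as field tests, so the 144 people tested outdoors may all have done both. The rule would then exclude nobody.

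The design also works against fitness-driven loss. Orthopedic restrictions that preclude the study activities are an exclusion criterion, and field testing follows a medical examination. "Intensity on the 8-km hike will be moderate", within a heart rate range set from each person's own thresholds, and no time limit is stated. Losses unrelated to fitness are plausible too: "The 1-km CTTT and 8-km hikes will be performed on 2 days" where possible, and tests are postponed above 26°C. A reader might infer that the rule does select fitter people. The documents do not support that; they support only that it may.

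A reader might also infer that the primary analysis becomes underpowered. That does not follow. The sample size already asks for 123 people to finish the study, and finishing means all three tests, so the 15% allowance covers this rule.

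Finally, a common cohort has some logic, because the CTTT prediction feeds the 8-km intensity recommendations. That supports reporting the three-test completers. It does not support dropping valid laboratory-plus-CTTT pairs from a model that needs nothing else. Nor is the rule a detail left to an unseen analysis plan: the article states it outright.

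**Conclusion.** The point holds as a mismatch between the stated analysis set and the primary model. The set requires a test that the model does not use, and the reason given does not explain why, since the model's field test is the CTTT. Any valid laboratory-plus-CTTT pair without a completed 8-km hike is lost needlessly.

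How many pairs are lost, and whether the loss is related to fitness, cannot be determined. Neither the completion count nor the reasons are given, and the loss may be zero. The 0.24 SD of extra over-prediction should be read as an upper bound for a 10% fitness-driven loss, because it lets fitness alone decide who is missing. The 10% and the R2 of 0.60 are assumptions. The full 0.94 SD should not be attributed to the rule: 0.70 SD is ordinary regression to the mean and remains when everyone is included. Power is a side issue. The reason to act is representativeness at the low end of fitness.

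**What to change.** Replace the single per-protocol set with sets defined by outcome:
- **Primary VO2max model:** all participants with a valid laboratory test and a valid CTTT, whatever happened on the 8-km hike.
- **Section-intensity outcome:** all participants with usable 8-km data.
- **Sensitivity analysis:** the primary model refitted in those who completed all three tests.

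Report how many people did the CTTT but did not complete the 8-km hike, with reasons, so that readers can judge whether the two sets differ in fitness.

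The cost is about one sentence in the analysis section and one extra model fit. No new data are needed.
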